### EQ-5D (Euroqol-5D)

The EQ-5D-3 L is a validated, generalized, quality of life questionnaire consisting of 5 domains related to daily activities with a three-level answer possibility. The EQ-5D-3 L obtains information pertaining to the current health status of the participant and measures physical, emotional and social status. The combination of answers leads to a total quality of life score.

### Short form disabilities of arm, shoulder and hand score (QuickDASH)

The QuickDASH is a shortened version of the DASH Outcome Measure. The QuickDASH uses 11 items to measure physical function and symptoms in people with musculoskeletal disorders of the upper limb. The QuickDASH also has two optional modules intended to measure symptoms and function in athletes, performing artists and other workers whose jobs require a high degree of physical performance. These optional models are scored separately. Both the QuickDASH and the full DASH Outcome measure are valid, reliable and responsive and can be used for clinical and/or research purposes [18].

### VAS

The Visual Analogue Scale assesses wrist pain and satisfaction in relation to the distal radius fixation. Participants are requested to mark their response on the 10 cm line (0–100) with a single slash (/). VAS Scales, especially for pain, are widely used and reported.

### Grip strength

Grip strength will be assessed using a Jamar Dynamometer. Three measurements for both the affected and non-affected arms will be recorded and an average of the three measurements will be used in the data analysis.

### Range of movement

Standard goniometric assessment of passive and active wrist movement will be completed according to the American Clinical Guidelines for Assessment of wrist movement. A standard medium sized wrist goniometer will be used.

### Radiographic evaluation

Standard posterior-anterior, lateral and oblique radiograph projection views will be taken to confirm diagnosis pre-operatively. X-rays will then be routinely performed as per the standard level of care to assess for union, standard radiographic parameters and hardware complications. An additional x-ray will also be taken at 24 months post-operation to assess for malunion, radiographic parameters and hardware complications.

These outcomes will be administered by a blinded assessor at the timeframes detailed in Table 3:

**Table 3 T3:** Intervals for outcome measures

**Assessment**	**Baseline**	**2 weeks**	**6 weeks**	**3 months**	**6 months**	**1 year**	**2 years**
**PRWE**			X	X	X	X	X
**Patient satisfaction**			X	X	X	X	X
**Pain**		X	X	X	X	X	X
**Radiological outcomes**	X	X	X	*	*	*	X
**AROM**		X	X	X	X	X	X
**Complications**		X	X	X	X	X	X
**EQ5D**	X		X	X	X	X	X
**Quick DASH**			X	X	X	X	X
**Grip strength**				X	X	X	X

*Only if required as part of treatment/normal care.

#### Sample size

Recruitment of a total of 130 participants (65 in each group) is anticipated to take approximately 104 weeks (assuming a 75% recruitment rate of eligible participants) based on historical emergency department presentation rate of this patient group. After allowing for a 30% loss to follow up, this investigation has 95% power to detect a between group mean difference in the primary outcome function (PRWE) of 10 (SD-15).

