## Abstract

**Background:**

Distal radius fractures are among the most common fractures seen in the hospital emergency department. Of these, over 40% are considered unstable and require some form of fixation. In recent years with the advent of low profile plating, open reduction and internal fixation (ORIF) using volar plates has become the surgical treatment of choice in many hospitals. However, it is currently unknown which plating system has the lowest complication rate and/or superior clinical and radiological outcomes following surgery. Few studies have compared different types of plates, which may have various features, different plate and screw designs or may be manufactured from different materials (for example, stainless steel or titanium). This study will specifically investigate and compare the clinical and radiological outcomes and complication rates of two commonly used volar plating systems for fixation of distal radius fractures: one made from stainless steel (Trimed™ Volar Plate, Trimed™, California, USA) and the other made from titanium (Medartis® Aptus Volar Plate, Medartis®, Basel, Switzerland). The primary aim of this study is to determine if there is a difference on the Patient Reported Wrist Evaluation six months following ORIF using a volar plate for adult patients with a distal radius fracture.

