#### Statistical analysis

Baseline demographic and clinical data will be reported using descriptive statistics and tabulated (e.g. Students *t*-test for continuous variables and Pearson chi-square for categorical variables). Between group differences in baseline data will be examined using unpaired conventional tests of hypothesis (such as unpaired t-tests) depending on the nature of the data. Between group and within group differences in outcome measures over time will be examined using a priori unpaired and paired conventional tests of hypothesis (such as Analysis of Variance with simple effects examined using t-tests) depending on the nature of the data. Bonferroni adjustments for multiple comparisons will be made where appropriate to mitigate risk of type-1 error. The complication rates will be reported in terms of frequency. The frequencies of complications will be compared using statistical analysis such as the Pearson chi-square statistic. For missing data values at different time points, a mixed linear regression model for repeated measures will be performed. Subanalysis for age will be undertaken to account for patients with osteoperotic bone.

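### The stated 95% power after 30% loss to follow-up is not reached by either conventional 5% test: about 88% two-sided and about 93.5% one-sided, with alpha and sidedness unstated

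*Protocol article*

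**What the plan says.** The Sample size section of the protocol article fixes almost every input:

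- Size: "Recruitment of a total of 130 participants (65 in each group").
- Loss and power: "After allowing for a 30% loss to follow up, this investigation has 95% power to detect a between group mean difference".
- Effect and spread: "in the primary outcome function (PRWE) of 10 (SD-15").

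The wording makes the 95% a figure that applies after the loss, not before it. Alpha and sidedness appear neither here nor elsewhere in the article.

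Three other places bear on the test. The Abstract frames the aim without direction: "The primary aim of this study is to determine if there is a difference on the Patient Reported Wrist Evaluation six months following ORIF". The Statistical analysis section plans conventional methods, "such as Analysis of Variance with simple effects examined using t-tests", and adds: "Bonferroni adjustments for multiple comparisons will be made where appropriate to mitigate risk of type-1 error". Table 3 schedules the PRWE from 6 weeks to 2 years, with no baseline measurement.

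**The concern.** The stated inputs should reproduce the stated power, and on the usual two-sided 5% reading they do not. The gap is six to seven percentage points, too large to be rounding.

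It matters because the research question at the end of the Background section asks whether the two plates give the same outcomes. A finding of no difference is therefore a plausible and consequential result. A reader who trusts the Sample size section would credit such a result with a 5% chance of having missed a 10-point difference. At two-sided 5% with the planned loss, that chance is about 12%.

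**Working it through.** **Inputs.** From Sample size: 65 per group recruited, 30% loss, difference 10, SD 15, so the standardised difference is 10/15 = 0.667. Alpha is assumed to be 5%, because none is given. Both sidedness options are shown.

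**Number analysed.** 130 × 0.7 = 91, or 65 × 0.7 = 45.5 per group.

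**Can the stated 95% be reproduced?** For n per group, the noncentrality is (10/15) × √(n/2). At n = 45.5 this is 0.667 × √22.75 = 3.18.

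- Normal approximation, two-sided 5%: Φ(3.18 − 1.96) = Φ(1.22) = 88.9%.
- Normal approximation, one-sided 5%: Φ(3.18 − 1.645) = Φ(1.535) = 93.8%.

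With the noncentral t distribution, which matches the planned t-test:

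| Analysed per group | Two-sided 5% | One-sided 5% |
|---|---|---|
| 45 | 87.9% | 93.2% |
| 45.5 (30% loss) | 88.2% | 93.5% |
| 46 | 88.6% | 93.7% |
| 50 | 91.0% | 95.2% |
| 65 (no loss) | 96.5% | 98.4% |

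At 30% loss neither column reaches 95%. The one-sided figure comes within two points.

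**Size needed for 95% at two-sided 5%.** n = 2 × (1.96 + 1.645)² × (15/10)² = 58.5, so 59 per group by the normal approximation and 60 by the t-test (95.2%). Allowing for 30% loss, 60/0.7 = 85.7, so 86 per group or 172 in total.

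**Loss that 130 can absorb at two-sided 5%.** 1 − 60/65 = 7.7% by the t-test, or 1 − 59/65 = 9.2% by the normal approximation. Directly, 8% loss gives 95.1%, 10% gives 94.7% and 15% gives 93.5%.

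**A possible origin of 130.** A one-sided 5% t-test needs 50 per group for 95% power, and 50 × 1.3 = 65. This matches the stated size exactly, but it is conjecture. It would also misapply the loss allowance: the correct step is 50/0.7 = 71.4, so 72 per group, and 65 recruited with 30% loss leaves 45.5, fewer than 50.

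**Adjustments that could move the figure.** With no baseline PRWE in Table 3, no gain from baseline adjustment can be credited. If a Bonferroni correction reached the primary comparison, power would fall. As an illustration, two-sided 1% with 45.5 per group gives about 71%.

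**The case against.** The strongest reply is that the 88% rests on an assumption. With alpha and sidedness unstated, a one-sided 5% test gives 93.5%, close to the claim, and a one-sided calculation can generate 130 exactly. This stands to the extent that 88% must always be quoted with its condition. It does not rescue the 95%: the one-sided figure still falls short, the route to 130 mishandles the loss, and a one-sided test does not fit an aim that names no direction.

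A second reply is that 88% describes a simple comparison at one visit among completers. The PRWE is collected at five visits, and a mixed model is planned for missing values, so a participant absent at 6 months may still contribute. The 30% is not tied to a visit either; if it is the loss by 2 years, more than 91 may be available at 6 months. These are fair qualifications. However, the Sample size section itself applies the 30% to its power claim, the stated aim is at 6 months, and the document gives no correlation or visit-specific loss from which a higher figure could be derived.

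A reader might also infer that the claim holds only if almost nobody is lost, or that the trial is underpowered. The figures support neither. About 8% loss is tolerated at two-sided 5%, and about 88% power after 30% loss is still above the common 80% benchmark.

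**Conclusion.** The power sentence is wrong as written under either conventional 5% test. With 91 analysed, a difference of 10 and SD 15, power is about 88% two-sided (type II error about 12%, some 2.4 times the implied 5%) and about 93.5% one-sided. The two-sided figure is the natural reading given the aim and planned tests, but it is conditional on alpha of 0.05, a simple two-group t-test, and the 30% loss applying at the primary time point.

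This is a correction that should be made to a stated number. It does not undermine the design: the recruitment target, randomisation, endpoint and analysis are unaffected.

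**What to change.** State the alpha and sidedness in the Sample size section and restate the power to match. If the sponsor confirms a two-sided 5% test, the sentence could read: *With 130 randomised and 30% loss (about 45 per group analysed), the trial has about 88% power at two-sided alpha 0.05 to detect a 10-point PRWE difference at 6 months (SD 15); with no loss, about 96%.* If another level or a one-sided test was intended, the sponsor should say so, justify it against the non-directional aim, and give the power for that choice.

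The cost is one sentence and a less favourable stated power. No extra enrolment is needed. Only a sponsor wishing to keep 95% after 30% loss at two-sided 5% would have to recruit about 172.

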#### Randomisation

Patients providing written informed consent for participation in this trial will be randomly assigned to either early intervention group (titianium or stainless steel volar multi-axial locking plates). The randomisation sequence will be computer generated and concealed in sequentially numbered sealed, opaque envelopes by a person, not otherwise associated with this research, to eliminate any risk of randomisation/recruitment bias. Each envelope will contain a sheet of paper with the words either “TITANIUM” or “STAINLESS STEEL”. This randomisation process will occur at the time of surgery booking.

#### Statistical analysis

Baseline demographic and clinical data will be reported using descriptive statistics and tabulated (e.g. Students *t*-test for continuous variables and Pearson chi-square for categorical variables). Between group differences in baseline data will be examined using unpaired conventional tests of hypothesis (such as unpaired t-tests) depending on the nature of the data. Between group and within group differences in outcome measures over time will be examined using a priori unpaired and paired conventional tests of hypothesis (such as Analysis of Variance with simple effects examined using t-tests) depending on the nature of the data. Bonferroni adjustments for multiple comparisons will be made where appropriate to mitigate risk of type-1 error. The complication rates will be reported in terms of frequency. The frequencies of complications will be compared using statistical analysis such as the Pearson chi-square statistic. For missing data values at different time points, a mixed linear regression model for repeated measures will be performed. Subanalysis for age will be undertaken to account for patients with osteoperotic bone.

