#### Outcome measures

A suite of outcome measures recommended and previously used in research for this patient group will be used [7,9,13]. A summary of these outcome measures and the tool used are detailed in Table 2.

**Table 2 T2:** Outcome measurement tools

**Outcome**	**Assessment**
Function	Patient rated wrist evaluation*
Disability	Disabilities of the arm, shoulder and hand
Health-related quality of life	EQ-5D-3 L (Australian)
Pain	Visual analogue scale
Satisfaction	Visual analogue scale
Grip strength	Jamar dynamometer
Range of movement	Goniometric evaluation
Radiological outcomes	Study specific generated checklist
Adverse events	Study specific generated checklist

*Primary outcome measure.

Patient demographic information and baseline (pre-injury) functional status will be collected after consent to take part in the trial. Structured information regarding other injuries which may affect outcome e.g. disruption of the carpal ligaments, will be collected but all patients will be included in the analysis.

The primary outcome measure for this study is the:

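### The six-month PRWE comparison names no covariate: baseline data go into significance tests and age into a separate subanalysis, neither of which adjusts the treatment comparison

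*Protocol article*

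**What the plan says.** All of the following is in the protocol article.

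- **Baseline data, Statistical analysis:** "Between group differences in baseline data will be examined using unpaired conventional tests of hypothesis". The same section also promises a descriptive baseline table.
- **Outcome comparison, Statistical analysis:** unpaired and paired tests, "such as Analysis of Variance with simple effects examined using t-tests". A mixed linear model is mentioned for missing values. Neither sentence names a covariate.
- **Age, Statistical analysis:** "Subanalysis for age will be undertaken to account for patients with osteoperotic bone".
- **What is collected, Outcome measures:** demographics are recorded, and "baseline (pre-injury) functional status will be collected after consent to take part in the trial". The instrument for pre-injury function is not named.
- **Schedule, Table 3:** of the patient-reported measures only EQ-5D has a baseline mark. PRWE and QuickDASH start at 6 weeks.
- **Sample size:** "Recruitment of a total of 130 participants (65 in each group"); "After allowing for a 30% loss to follow up", the study is said to have "95% power to detect a between group mean difference in the primary outcome function (PRWE) of 10 (SD-15").
- **Aim, Abstract:** to "determine if there is a difference on the Patient Reported Wrist Evaluation six months following ORIF".

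**The concern.** Three stated choices work poorly together.

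First, a significance test of baseline balance does not help the PRWE comparison. A small p-value does not remove an imbalance, and a large one does not show that there is none.

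Second, the age subanalysis is meant to account for osteoporotic bone. Examining results by age may describe whether the plates perform differently at different ages. It leaves the overall difference between plates unadjusted for age.

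Third, the outcome comparison as described uses no baseline information, although age and pre-injury function will be on file. The Randomisation section describes no stratification, so on the text shown nothing in the design balances age between arms.

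At stake are some precision in the primary comparison and protection against chance imbalance in a trial expected to analyse about 91 patients.

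**Working it through.** **Inputs.** From Sample size: 65 per arm, 30% loss, difference 10, SD 15. Evaluable per arm: 65 × 0.70 = 45.5, or 91 in total. Alpha and sidedness are not stated. I assume 0.05, and two-sided because the aim is to find a difference. The correlation of baseline variables with six-month PRWE is not given, so R is assumed over the range 0 to 0.5.

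**Step 1: the plan's own power figure.** Power = Φ(δ / (σ√(2/n)) − z).

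With n = 45.5, √(2/45.5) = 0.2097, and 10 / (15 × 0.2097) = 3.180.

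- Two-sided 0.05: Φ(3.180 − 1.960) = Φ(1.220) = 88.9% (88.2% with the t distribution).
- One-sided 0.05: Φ(3.180 − 1.645) = Φ(1.535) = 93.8%.
- Two-sided with no loss, 65 per arm: 96.7%.
- Loss taken as 65/1.3 = 50 per arm: 91.5% two-sided, 95.4% one-sided.

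The stated 95% is approached only with a one-sided test or by ignoring the loss. Under the two-sided reading there is a shortfall of about 6 points, so recovered precision would be useful.

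**Step 2: effect of adjustment.** Replace σ by 15√(1 − R²), keeping n = 45.5 per arm, two-sided 0.05.

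| Assumed R | R² | Residual SD | Power | 1/(1 − R²) |
|---|---|---|---|---|
| 0 | 0 | 15.00 | 88.9% | 1.00 |
| 0.1 | 0.01 | 14.92 | 89.2% | 1.01 |
| 0.2 | 0.04 | 14.70 | 90.1% | 1.04 |
| 0.3 | 0.09 | 14.31 | 91.5% | 1.10 |
| 0.4 | 0.16 | 13.75 | 93.4% | 1.19 |
| 0.5 | 0.25 | 12.99 | 95.7% | 1.33 |

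The last column is the equivalent multiple of the sample size.

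To reach 95% two-sided, the residual SD must be 10 / (0.2097 × (1.960 + 1.645)) = 13.2. That is R² = 1 − (13.2/15)² ≈ 0.22, or R ≈ 0.47.

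**Step 3: cost if the covariates explain nothing.** With 45 per arm and two useless covariates, t-based power goes from 87.85% to 87.84%.

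**Step 4: cost of dropping patients with missing covariates.** If a fraction m is dropped, the effective sample size is multiplied by (1 − m)/(1 − R²). The gain is cancelled at m = R²: 4% missing at R = 0.2, 9% at R = 0.3. A rule for missing covariate values is therefore needed.

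**Step 5: chance imbalance.** The standard error of a standardised covariate difference between arms is √(2/45.5) = 0.21. A difference of at least 0.2 SD either way has probability 2 × (1 − Φ(0.2/0.21)), about one in three.

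**The case against.** The strongest objection is that a condensed article need not list covariates. The section is worded loosely, the mixed model could carry them, and the Rehabilitation section says that deviations from the study protocol will be controlled for. That stands in part: silence about covariates alone would be no finding, and a fuller document may name them. It does not rescue the two things that are stated, namely the baseline tests and a subanalysis offered as the way to account for age. Rehabilitation deviations also arise after randomisation and are no substitute for a baseline covariate.

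Several stronger readings are tempting, and the article does not support them.

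- **That adjustment is known to give a substantial gain.** The article gives no correlation. No baseline PRWE, usually the strongest covariate, is scheduled. The pre-injury instrument is unnamed, and it is not said whether baseline EQ-5D refers to the time before or after injury. At R of 0.2 or below the gain is about 1 point or less.
- **That the baseline tests examine a null hypothesis known to be true.** That holds for everyone randomised. Here patients are randomised at surgery booking, those found intra-operatively to need additional fixation are then removed, and 30% loss is allowed for. The analysed set may be unbalanced for reasons other than chance. The tests remain a poor tool, because at this size they would miss much of it and they correct none of it.
- **That age will be handled by two underpowered strata.** The article mentions no cut-point, strata or within-stratum tests. An interaction term would itself be a subanalysis for age.
- **That baseline data have no other use.** Baseline EQ-5D could enter the within-group comparisons over time.

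An interaction test in about 91 patients also has low power, so it should be exploratory. Age should be centred, otherwise the plate coefficient becomes the effect at age zero.

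**Conclusion.** The point holds as a recommendation to replace stated choices with better ones. The baseline tests do not serve the comparison, and a subanalysis does not adjust the overall PRWE difference for age. Pre-specified adjustment for age is a better method at almost no cost.

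The size of the benefit is uncertain: from nothing at R = 0 to about 7 points of power at R = 0.5, with about 1 point at R = 0.2. These figures assume a two-sided 0.05 test, 45.5 evaluable patients per arm, SD 15 and no patients lost through missing covariates. Adjustment should not be counted on to restore the stated 95% power, since that needs R of about 0.47.

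**What to change.** 1. Delete the baseline hypothesis tests and keep the descriptive table by arm.
2. Pre-specify age, as a continuous variable, as a covariate in the primary six-month PRWE model, whatever balance is observed. Add pre-injury functional status where it is reliably recorded, and name the instrument.
3. Use baseline EQ-5D as a covariate only if its reference time, before or after injury, is clear.
4. State a simple rule for missing covariate values so that no patient leaves the analysis on that account.
5. If effect modification by age is of interest, fit one plate-by-age interaction, with age centred, in a secondary model labelled exploratory.

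The cost is analysis wording. Age needs no new data, and the loss of degrees of freedom is negligible.

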**Methods/Design:**

This study will implement a randomized prospective clinical trial study design evaluating the outcomes of two different types of volar plates: one plate manufactured from stainless steel (Trimed™ Volar Plate) and one plate manufactured from titanium (Medartis® Aptus Volar Plate). The surgery will be performed at a major trauma hospital in Brisbane, Australia. Outcome measures including function, adverse events, range of movement, strength, disability, radiological findings and health-related quality of life will be collected at 6 weeks, 3, 6, 12 and 24 months following surgery. A parallel economic analysis will also be performed. This randomized clinical trial is due to deliver results in December 2016.

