### Patient rated wrist evaluation (PRWE)

The PRWE is a 15-item questionnaire designed to measure wrist pain and disability in activities of daily living. The PRWE allows patients to rate their levels of wrist pain and disability from 0 to 10, (0 = no difficulty, 10 = unable to do) and consists of 2 subscales:

1) PAIN subscale – 5 items.

2) FUNCTION subscale - 10 items (specific and usual activities).

In addition to the individual subscale scores, a total score can be computed on a scale of 100 (0 = no disability), where pain and function problems are weighted equally.

The PRWE is a standardized outcome tool that is easy to administer and score, and complements traditional impairment and radiographic measures. The PRWE has been used to assess wrist-related pain and disability in various populations and its reliability, validity, and responsiveness have been tested and reported in published studies [17].

The secondary outcome measures in this trial are the:

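### Baseline EQ-5D is scheduled, but no named between-plate method uses it; naming it as a covariate would sharpen this secondary comparison at almost no cost

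*Protocol article*

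**What the plan says.** **Schedule.** Table 3 marks EQ-5D at baseline, 6 weeks, 3 months, 6 months, 1 year and 2 years. PRWE, satisfaction and QuickDASH start at 6 weeks and pain at 2 weeks. Under Outcome measures the article adds "Patient demographic information and baseline (pre-injury) functional status will be collected after consent to take part in the trial", but it names no instrument for this and Table 3 has no row for it.

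**Role.** EQ-5D is in the list that opens with "The secondary outcome measures in this trial are the". Its own section says "The EQ-5D-3 L obtains information pertaining to the current health status of the participant".

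**Analysis.** For outcomes, the Statistical analysis section says "Between group and within group differences in outcome measures over time will be examined using a priori unpaired and paired conventional tests of hypothesis", followed by the examples "such as Analysis of Variance with simple effects examined using t-tests) depending on the nature of the data". For baseline data it says "Between group differences in baseline data will be examined using unpaired conventional tests of hypothesis (such as unpaired t-tests", and no action is tied to the result. It then adds "For missing data values at different time points, a mixed linear regression model for repeated measures will be performed". No covariate is named anywhere, and none is ruled out.

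**Economics.** The abstract says "A parallel economic analysis will also be performed" and gives no effect measure.

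**The concern.** A baseline measurement on the same scale as the outcome is often a useful covariate in a randomised comparison. For EQ-5D the plan will have one, yet the text gives it only two uses: a test of balance between the arms, and paired comparisons within an arm. Neither sharpens the plate contrast.

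Two things are at stake for quality of life. The confidence interval is wider than the data require. And if the arms happen to differ on EQ-5D at baseline, part of that difference carries through to each follow-up comparison. Testing balance without fixing what follows also leaves room for a decision to adjust after the baseline results are seen.

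**Working it through.** **Inputs from the article.** 130 participants, 65 per arm, 30% loss to follow-up (Sample size). That leaves 130 × 0.7 = 91, or 45.5 per arm; 45 is used below. The article gives no EQ-5D standard deviation, target difference, power or correlation, so there is no EQ-5D figure to reproduce. Its one power statement concerns PRWE and does not enter here.

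**Assumptions.** Two-sided 5% level; normal approximation; linear baseline-to-follow-up correlation rho, equal in both arms, varied from 0.1 to 0.7.

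**Formulas**, in units of the EQ-5D standard deviation:

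1. Unadjusted standard error of the plate difference: √(2/45) = 0.211.
2. With baseline as a covariate, the variance is multiplied by 1 − rho².
3. Equivalent unadjusted sample size per arm: 45 / (1 − rho²).
4. Power after adjustment, for an effect that has 80% power unadjusted: Φ[(1.960 + 0.842)/√(1 − rho²) − 1.960].
5. A chance baseline difference at its 95% limit is 1.96 × √(2/45) = 0.41 SD. The part expected to reach the unadjusted follow-up comparison is rho × 0.41.

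| rho | variance ratio | equivalent n per arm | 80% power becomes | carried imbalance (SD) |
|---|---|---|---|---|
| 0.1 | 0.99 | 45.5 | 80.4% | 0.04 |
| 0.2 | 0.96 | 46.9 | 81.6% | 0.08 |
| 0.3 | 0.91 | 49.5 | 83.6% | 0.12 |
| 0.4 | 0.84 | 53.6 | 86.4% | 0.17 |
| 0.5 | 0.75 | 60.0 | 89.9% | 0.21 |
| 0.7 | 0.51 | 88.2 | 97.5% | 0.29 |

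Worked line for rho 0.5: 1 − 0.25 = 0.75; 45/0.75 = 60; 2.802/0.866 − 1.960 = 1.275; Φ(1.275) = 0.899; 0.5 × 0.413 = 0.21.

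**Sensitivity to the loss figure.** The article does not say at which visit the 30% applies. The variance ratio does not depend on n. With all 65 per arm, the 95% limit for a chance baseline difference is 1.96 × √(2/65) = 0.34 SD instead of 0.41.

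**If baseline is entered as one more time point.** An ANOVA over time could include it. The arm-by-time contrast against baseline is then a comparison of changes. With equal SDs at both times, its variance relative to the unadjusted follow-up comparison is 2(1 − rho): 1.4 at rho 0.3 and 1.0 at rho 0.5, against 0.91 and 0.75 for covariate adjustment. The t-tests for simple effects at each visit still ignore baseline.

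**The case against.** The strongest reply is that the article does not commit to an unadjusted EQ-5D analysis. Its methods are open examples covering all outcomes and depend on the data. The mixed model is already named, will probably be needed with 30% loss, and could carry baseline EQ-5D. Covariate lists for secondary outcomes usually sit in the analysis plan, which is not shown. This stands in part: a reader might infer that the plan has ruled out baseline adjustment, and the text does not support that. What remains is that the methods it does name make no use of a baseline value it schedules, and that the mixed model is tied to missing data alone. A specific better choice is available from data already planned.

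Three other inferences also go too far:

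- **That chance imbalance biases the result.** It causes no bias on average and no inflation of type I error; the unadjusted standard error already allows for it. Only precision, and the estimate conditional on the imbalance observed, are affected.
- **That the gain is known to be material.** It rests on an unstated rho. At 0.2 or below, the saving is 4% of variance or less. Rho may well be low if the baseline form captures the days after an acute fracture. The wording on current health status hints at that, while the baseline functional status is described as pre-injury. The article does not settle which state EQ-5D refers to.
- **That the economic results are compromised.** No utility or quality-adjusted life-year measure is mentioned, so any link is conditional.

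**Conclusion.** The point holds as a modest improvement to a secondary analysis. The named between-plate methods leave the baseline EQ-5D unused, and no sentence commits the plan to using it. The unadjusted comparison is valid but gives up about 1% of variance at rho 0.1, 9% at 0.3 and 25% at 0.5. For an effect with 80% power, that means about 80%, 84% and 90% after adjustment. The gain reaches 5 percentage points only from a rho of about 0.4. These figures rest on an assumed correlation and a two-sided 5% level. The primary PRWE comparison is not affected: Table 3 gives PRWE no baseline score, and the trial is sized on PRWE alone.

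**What to change.** In the Statistical analysis section, state that the between-plate EQ-5D comparison at each follow-up visit comes from the repeated-measures mixed model already named (or from ANCOVA). Follow-up EQ-5D should be the outcome and baseline EQ-5D a covariate, included whatever the baseline balance tests show. Under Outcome measures or beside Table 3, state whether the baseline EQ-5D refers to the pre-injury or the post-injury state. If the economic analysis uses EQ-5D utilities, apply the same adjustment there.

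The cost is two or three sentences and about one degree of freedom. It needs no new patients, visits or measurements. If rho turns out low, little is gained and almost nothing is lost.
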